### 2.4. Randomization and blinding

The treatment allocation of EA, EAWN, or waitlist control for each eligible subject in the study will be determined through a randomization process. Participants will be told that they will be randomized to 1 of 3 groups: EA for 5 weeks followed by observation for 5 weeks; EAWN for 5 weeks followed by observation for 5 weeks; or observation for 10 weeks followed by EA or EAWN for 5 weeks. Treatment or assessment will be scheduled to avoid contact between the participants. The random allocation to the 3 arms of the study will be generated using Random Allocation Software,^[17]^ following a balanced 1:1:1 ratio. A standard block size of 6 will be used, which will not be revealed to the site investigators. This will be performed by an independent administrator who is not involved in the study, and the information on the random allocation list will remain strictly confidential. The randomization result will be kept in sequentially numbered, opaque, sealed envelopes to ensure allocation concealment. In this study, practitioners and patients will not be blinded; however, the outcome assessors will be blinded to the intervention assignment.

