#### 2.9.1. Primary outcome

Tinnitus loudness is a main symptom of tinnitus. The primary endpoint of our study will be the change in NRS score for tinnitus loudness from baseline to treatment completion (week 5). Changes in the mean NRS score for tinnitus from baseline to week 10 (5 weeks after treatment completion) will also be assessed. The NRS for the loudness of tinnitus is a widely used measurement for tinnitus.^[2]^ Subjects will rate the loudness of tinnitus using an 11-point NRS (0 − 10) with 0 indicating “no tinnitus”, and 10 indicating “maximum intolerable tinnitus”. The higher the score, the greater the tinnitus loudness and its effect.

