#### 2.9.2. Secondary outcome

Tinnitus handicap inventory (THI) will be used as the secondary outcome measurement. The THI is a commonly used self-report measure for evaluating the extent of tinnitus-related distress with good reliability and validity.^[30]^ In this study, the validated Chinese (Cantonese) version of the THI will be adopted.^[31]^ This questionnaire consists of 25 items and can be categorized into 3 subscales: functional (12 items), emotional (8 items), and catastrophic (5 items). Each item will be scored on a 3-point rating scale. A yes will score 4 points; sometimes, 2 points; and no, zero points. The total THI score range from 0 to 100, with a higher score indicating a greater impact of tinnitus on the patients quality of life.

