### 2.13. Statistical analysis

#### 2.13.1. Sample size calculation

The sample size calculation will be based on the primary outcome measure of the NRS score of the loudness of tinnitus (0 − 10 points) and performed using OpenEpi.^[35]^ An estimation of the between-group difference and standard deviation is necessary because of the lack of similar comparable studies. In this study, we assume that similar differences in the NRS score of tinnitus loudness will be detected between the EA and waitlist control groups or the EAWN and waitlist control groups. We presume that a clinically significant difference of mean 2-point reduction and standard deviation of 2.49 in the NRS score of tinnitus loudness is detected based on previous studies^[36,37]^ and expert opinion. Using a 2-sided test, an alpha value of 0.05, and a power of 80%, it is estimated that 25 subjects will be required per study group. Considering a 20% attrition rate, the sample size for each group will be 30 subjects, which implies a total sample size of 90 subjects for the entire trial.

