#### 2.13.2. Statistical method and analysis

Statistical analysis of the collected data will be performed using IBM SPSS Statistics 27 (IBM Corp, Armonk, USA). An intention-to-treat approach will be used in this study. All randomized subjects will be included in the analysis, regardless of whether they received treatment. In addition, interim analyses will not be performed.

Descriptive statistics will be used to summarize participants baseline characteristics by group using mean (standard deviation), median (interquartile range), or number (percentage) as appropriate. All measurement data will first be assessed using normality tests. One-way analysis of variance or Welch analysis of variance will be used for comparison among the 3 groups for continuous variables. Categorical variables will be compared using the Pearson chi-squared test (or Fisher exact test).

Analyses of the primary and secondary continuous outcome variables among the 3 study groups (EA, EAWN, and waitlist control) overtime (baseline, weeks 5 and 10) will be performed using linear mixed models for repeated measures analysis, with treatment, time point, and interaction between treatment and time point included as fixed effects, within-person correlation modeled as a random effect, and age and tinnitus duration adjusted as covariates in the model. Missing data will be processed using the mixed effects model, assuming missing at random. Significant results (significant interaction, time × study groups) will be subject to post hoc tests to determine which group scores differently. Mean differences at weeks 5 and 10 will be estimated by the treatment × time interaction term, with associated 95% confidence intervals and *P* values.

Comparisons between the EA and EAWN groups for the adverse event rate among the 3 groups will be evaluated using the Pearson chi-squared test (or Fisher exact test).

The results will be considered statistically significant at a probability level of *P* < .05 with a 2-sided test throughout the analysis. In post hoc tests, we will employ the Bonferroni correction method and appropriately adjust the overall level of significance for multiple primary and secondary outcomes at different time points.

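### The Bonferroni rule refers to several primary outcomes although there is one, and on its natural reading makes week-5 loudness share alpha with THI and week 10

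*Protocol article*

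**What the plan says.** Section 2.9.1 of the protocol article names a single primary endpoint at a single time point: "The primary endpoint of our study will be the change in NRS score for tinnitus loudness from baseline to treatment completion (week 5". Week 10 is an addition to it: "Changes in the mean NRS score for tinnitus from baseline to week 10 (5 weeks after treatment completion) will also be assessed". Section 2.9.2 gives one secondary outcome: "Tinnitus handicap inventory (THI) will be used as the secondary outcome measurement".

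Section 2.13.2 compares the three arms in a mixed model, with post hoc tests after a significant treatment-by-time interaction. It sets two-sided P < .05 as the general criterion. It then says that the post hoc tests will use Bonferroni and that the investigators will "appropriately adjust the overall level of significance for multiple primary and secondary outcomes at different time points". It gives no list of tests and no divisor.

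Section 2.13.1 sizes the trial for each active arm against waitlist, for a "clinically significant difference of mean 2-point reduction and standard deviation of 2.49 in the NRS score of tinnitus loudness". The level is not adjusted, and the number is for each arm: "Using a 2-sided test, an alpha value of 0.05, and a power of 80%, it is estimated that 25 subjects will be required per study". Enrolment follows from that: "Considering a 20% attrition rate, the sample size for each group will be 30 subjects".

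**The concern.** The endpoint sections rank the outcomes, and the multiplicity sentence ignores the ranking. There are no multiple primary outcomes to adjust for. If the sentence is followed as it most naturally reads, the threshold for week-5 loudness depends on how many secondary results are tested beside it. Being primary then has no effect on the decision.

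The sample size makes no allowance for such sharing, so the planned 80% power would not apply to the test actually used. Because the family is uncounted and the adjustment is promised only in general terms, the divisor could also be settled after the data are seen.

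The point is which tests belong in the family and in what order. The arithmetic of section 2.13.1 and the interaction condition are separate matters.

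**Working it through.** **Inputs.** Difference 2 points, SD 2.49, two-sided alpha 0.05, power 80%, 25 per group, 30 enrolled per group (section 2.13.1). Three arms, "following a balanced 1:1:1 ratio" (section 2.4). Two outcomes and two post-baseline visits (section 2.9).

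**The plan's own figure.** n = 2 × [2.49 × (1.960 + 0.842) / 2]² = 24.3, rounded up to 25 per group. It is reproduced.

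**Size of the family (assumed, since the text gives none).**
- Two active-versus-waitlist contrasts × 2 outcomes × 2 visits = 8 tests; threshold 0.05/8 = 0.00625.
- Three pairwise contrasts × 2 × 2 = 12 tests; threshold 0.05/12 = 0.00417.
- For comparison, week-5 NRS alone: 0.025 with two contrasts, 0.0167 with three.

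**Power for a true 2-point difference.** With 25 per arm, SE = 2.49 × √(2/25) = 0.704. Pooling the variance over three arms gives 75 − 3 = 72 residual df. The smallest significant difference is critical t × SE; power is from the non-central t distribution with non-centrality 2/0.704 = 2.84.

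| Rule for week-5 NRS | Threshold | Critical t | Smallest significant difference | Power per contrast |
|---|---|---|---|---|
| Unadjusted, as sized | 0.05 | 1.99 | 1.40 | 80.0% |
| 8 pooled tests | 0.00625 | 2.82 | 1.98 | 51.3% |
| 12 pooled tests | 0.00417 | 2.96 | 2.08 | 45.8% |

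The normal approximation gives the same picture: 81%, 54% and 49%. With all 30 per arm analysed, 12 tests still lower power from 87% to 57%.

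**Alternative: week-5 NRS in its own family, Holm over the two waitlist contrasts** (400,000 simulated trials, 25 per arm). Power is 76% per contrast and 68% for both. Pooled Bonferroni gives 35% (8 tests) or 30% (12 tests) for both. The family error of this step is 0.046 when both arms are null and 0.041 when one arm is null and the other has the planned effect.

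**Would an observed difference of exactly 2.0 be significant?**
- 25 per arm, 72 df: t = 2.84, P = 0.0059. It passes at 8 tests and fails at 12.
- 25 per arm, two-sample t test (48 df): P = 0.0066. It fails at 8 and 12.
- 24 per arm (30 less 20%), 69 df: P = 0.0070. It fails at 8 and 12.
- 30 per arm, 87 df: P = 0.0025. It passes even at 12.
- 6 tests or fewer (threshold 0.0083 or higher): it passes in every case above.

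**Moving on to the secondary tests.** The rule for doing so matters. Suppose one successful week-5 contrast were enough to open the next step for both arms. With one arm null, simulated family error is then about 0.06–0.07 at the planned effect in the other arm, and up to about 0.09 at a larger one. Requiring both contrasts to succeed keeps it at or below about 0.05.

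**The case against.** The strongest reply is that the pooled family is inferred. The text ties Bonferroni to post hoc tests, qualifies the adjustment as an appropriate one, keeps P < .05 as the general criterion and attaches 95% intervals to the week-5 and week-10 differences. It could mean Bonferroni over group pairs within each model, with the rest left to an analysis plan that is not shown. This stands in part: the 8 and 12 are assumptions. But the sentence itself is in the protocol, it names primary and secondary outcomes and time points together, and it conflicts with section 2.9. An analysis plan would have either to pool or to depart from it.

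A reader might infer that the rule makes an observed 2-point difference non-significant. The documents do not support that in general. It takes the 12-test family, or 8 tests with slightly fewer patients or df. A modest gain in precision from the covariates would also remove it: if they explained 9% of the variance (an assumption), P at 25 per arm would be about 0.0040, just below 0.00417.

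A reader might also infer that a true planned effect is more likely missed than found. At 25 per arm that holds with 12 tests (46%) but not with 8 (51%).

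Finally, Bonferroni across endpoints is valid, and it allows a THI claim even if loudness fails. That is a real advantage of pooling. It is bought with roughly 25 to 30 percentage points of power per contrast on the endpoint for which the trial is sized.

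**Conclusion.** The concern holds as an inconsistency with a material cost on the natural reading. Section 2.13.2 adjusts for several primary outcomes where section 2.9.1 has one, and does not keep that one apart from the secondary tests. If the tests are pooled, power per contrast at week 5 is about 46–51% instead of 80%, against about 76% when the two primary contrasts form their own family.

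The power loss is the firm consequence. The reversal of an observed 2-point result is possible but narrow, and is not a general property of the rule.

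These figures assume a family of 8 to 12 tests, that SD 2.49 applies to the analysed week-5 contrast, that the mixed model gives about the same standard error as a comparison of two means, and 25 analysed per arm. They leave out the interaction test that precedes the post hoc tests. Requiring it as well could only lower them.

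**What to change.** In section 2.13.2, delete the reference to multiple primary outcomes and replace the pooled adjustment with a stated order:

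1. Week-5 NRS change, EA versus waitlist and EAWN versus waitlist, in their own family at overall two-sided 0.05, with Holm over the two contrasts.
2. Week-10 NRS, then THI at week 5, then THI at week 10. Each is tested at overall 0.05 with Holm over the same two contrasts, and only if both contrasts at the preceding step are significant. If the sponsor prefers to proceed arm by arm, the procedure should first be shown to hold the family error at 0.05.
3. EA versus EAWN reported as an estimate with its confidence interval.

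The cost is wording in the protocol and the analysis plan, with no added patients or visits. The downside is that THI and week-10 results can be claimed as confirmed only after the primary succeeds; otherwise they are reported as estimates with intervals.

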### 2.14. Study monitoring and quality control

To guarantee the quality of the study, advance training will be carried out before subject recruitment to ensure that all investigators and related staffs adhere to the study protocol. The investigators will assure that all reported trial data are accurate, complete, and verifiable from the source documents. To oversee the progress of the study, quarterly monitoring meetings will be held between the investigators and the Hospital Authority Chinese Medicine Department, which is completely uninvolved in the running of the trial and has no competing interests.

### 2.15. Patient and public involvement

Participants and the public will not be involved in the design, development, recruitment, or conduct of this clinical trial.

### 2.16. Ethical consideration and dissemination plans

The study will be conducted in compliance with local law and will be carried out in accordance with the ethical principles of the Declaration of Helsinki^[38,39]^ and the ICH-GCP guidelines. Prior ethical approval (CREC Ref. No. 2022.327-T) has been obtained from the Joint Chinese University of Hong Kong − New Territories East Cluster Clinical Research Ethics Review Committee before the commencement of the study. Any changes to the protocol will be reported to this committee, and amendment approval should be obtained before any changes can occur. Each participant will voluntarily sign an informed consent form before participation. This study is registered at ClinicalTrials.gov (Identifier: NCT05557357). We plan to publish the results of this clinical trial in a peer-reviewed medical journal or academic conference proceedings.

## 3. Discussion

Tinnitus is a condition characterized by the perception of a persistent or intermittent sound without an external sound source. It is an invisible condition and a common otologic disorder that can be exasperated. It is a burdensome condition at both individual and societal levels. However, tinnitus treatment remains challenging.

Acupuncture and moxibustion have been used in otorhinolaryngology to treat tinnitus for thousands of years by regulating the flow of *qi* and blood in the body.^[10]^ A previous study reported that acupuncture can cause an effect on the cochlear function in patients with tinnitus, with a significant change in the amplitude of otoacoustic emissions.^[40]^ It can also affect the contralateral ear through the medial olivocochlear system, which may lead to tinnitus regression. Moreover, through needling in the periauricular region, the effect of acupuncture on tinnitus was associated with an improvement in cochlear blood flow via the infrared thermography test.^[41]^ In addition, acupuncture may have an effect on tinnitus by adjusting the central neurotransmitters gamma-aminobutyric acid and 5-hydroxytryptamine content.^[42]^ However, due to the heterogeneity of previous studies and limitations in trials with high levels of evidence, positive findings cannot be generalized, and the results are not conclusive.^[11,14]^

This study is a rigorously designed evidence-based clinical trial to evaluate whether EA or EAWN has therapeutic effects in reducing tinnitus loudness and improving tinnitus disability. The trial focus on 50 to 70 years old patients as these age groups have a higher prevalence of tinnitus.^[5]^ Carefully designed treatment procedures are developed, and proper training will be provided to participating practitioners for standardization of intervention for both treatment groups. Besides, validated and frequently used outcome measures of the NRS and THI will be used.^[43]^ Loud tinnitus is one of the most frequent clinical complaints of patients with tinnitus. NRS is commonly used to provide numeric estimates of tinnitus loudness. Subjective loudness can simply and quickly measure loudness and distress in patients with tinnitus^[44]^ and will be set as the primary outcome measure. In addition, the THI is a validated and specific questionnaire that measures the impact of tinnitus on daily life and symptom severity. Moreover, the THI has been proven to yield excellent internal consistency and reliability, and significant correlations have been found between the THI and symptom rating scales.^[30]^ By using these validated instruments, proper treatment results will be generated.

Nevertheless, this study has some limitations. Owing to the nature of the intervention, it is difficult to develop proper blinding for participants and practitioners on electroacupuncture and warm needling, which may lead to a high risk of performance bias. Moreover, the use of self-reported and subjective assessment tools may introduce bias or variability in the outcome measures. In addition, limited resources will only allow for 5-week posttreatment follow-up assessments, and the longer-term effects of the 2 interventions will not be evaluated.

## 4. Conclusion

This protocol describes the details of a randomized controlled clinical trial for tinnitus. The findings from this proposed randomized controlled trial will provide additional clinical evidence on whether EA or EAWN could be of value for the management of tinnitus among older adult patients, and facilitate clinical practice and scientific studies in the future.
